### **3.2 Investigational Product (treatment, device) and Indication**

Not applicable, since we are evaluating a concept, which is already in routine use, not a device.

### **3.3 Clinical Evidence to Date**

All relevant available evidence is summarized under 3.1

### **3.4 Dose Rationale: Rationale for the intended purpose in study**

High Flow (70 l/min): THRIVE is normally used with very high flows, this is standard procedure

Medium Flow (10 l/min): Every anaesthetic respirator or oxygen wall connection can provide

10 l/min, which in emergency situation would be superior due to its higher availability.

Low Flow (2 l/min): Low flows could even be used with dry oxygen. This would reduce cost even further, and could find application in prevention of desaturation in high risk situations.

### **3.5 Explanation for choice of comparator (or placebo)**

Our control group consists of standard of care use when using HFNCT. They will receive 70l/min using continuous laryngoscopy as it has been established by Patel et al. [2]. We will not use a placebo (which could be air (21% oxygen)) for this study, as this would lead to desaturation within a few minutes and is not standard of care.

However, HFNCT is not standard of care during anaesthesia induction as patients normally receive mask-preoxygenation, mask ventilation and tracheal intubation while the apnoea period is kept as short as possible.

### **3.6 Risks / Benefits**

Low-flow oxygen is being used every day to virtually every patient on medical wards, intensive care units or postoperative care units, and in the operating theatre. High-flow oxygen is being used in adult anaesthesia practice for a few years now with oxygen flow rates of 0.5-70 l/min in the operating theatre during anaesthesia, and have very little complications.

Drying of the nasal mucosa can cause discomfort in patients with prolonged nasal cannula therapy, especially if the oxygen is not humidified [15]. We will provide pre-nasal cannulas which have been shown to be less likely to cause discomfort [16]. Additionally, we will only use humidified oxygen. Patients receiving high flow will also profit from additionally heated oxygen delivery, which even further reduces nasal irritations.

Further risk is due to placement of an arterial catheter (e.g. obstruction of vessel or bleeding). Risks are overall extremely low [17]. Risk factors for complications include peripheral occlusive arterial disease, but we exclude these patients from our study, further reducing risk of complications. Also, an experienced anaesthetist will place this cannula to minimize risk for multiple attempts.

For an arterial blood gas analysis, very little blood is needed, and we estimate to take a maximum of 75 ml of blood in total from each patient. As we have excluded all patients with haemoglobin < 100 g/l, this amount can be considered haemodynamically irrelevant and will not trigger transfusion during surgery.

A very small risk for mucosal bleeding occurs, when passing the nasopharyngoscope through the nose, to obtain view of the larynx. In normal preoperative airway assessment this procedure is regularly performed on awake patients and we have never witnessed a mucosal bleed. Nevertheless, this will be further reduced, by having a properly trained and well experienced operator performing this task.

EIT, NIRS, NarcotrendTM, heart rate, and transcutaneous capnography are all very standard, non-invasive measurements that can be obtained in an extremely safe manner.

### **3.7 Justification of choice of study population**

The study participants are of all ages and genders. We want a heterogenic population presenting to the operating theatre each day. We exclude patients who are too sick to safely undergo our experiment or who could bias our physiological findings with their underlying disease.

For more see 7.1: eligibility criteria.

## **4. STUDY OBJECTIVES**

### **4.1 Overall Objective**

This study investigates under controlled conditions the concept of nasal cannula therapy at different flow rates to prolong the apnoea time during induction of anaesthesia. We hope to provide evidence that can further improve the safety of airway management in adult patients. This study will enable us to quantify the physiological effects of high-flow nasal cannula therapy and help us to distinguish it better from conventional medium and low-flow apnoeic oxygenation. Especially differences in  $p_{tc}CO_2$  will be observed and compared in order to determine the effect of nasal flow on  $CO_2$  clearance as well as the effects of elevated  $CO_2$  levels on vital parameters.

### **4.2 Primary Objective**

Primary study objective is to evaluate the mean increase of transcutaneous  $CO_2$  ( $p_{tc}CO_2$ ) in mmHg/min.

### **4.3 Secondary Objectives**

Secondary study objective is to evaluate the mean duration of apnoea. Also, changes in EIT, NIRS, BP and heart rate are measured. We will also assess airway patency while performing jaw thrust. This can be either patent or not-patent.

We also want to monitor the effect of increased  $CO_2$  on the cardiac output via the simultaneously obtained pulse contour analysis using either FlowTrac by Edwards Lifescience, Irvine, California, or LiDCO by LiDCO Ltd, London, UK.

Bilateral frontal cerebral NIRS measurements will be performed to determine the effect of high  $CO_2$  on brain perfusion. A NIRO monitor by Hamamatsu, Japan, will be used, which delivers brain oxygenation as a surrogate of brain perfusion, as well as the percentage of oxygenated and deoxygenated blood in the sampled tissue.

To ensure absence of respiratory movements, complete neuromuscular blockage will be confirmed using train-of-four (TOF) which should be 0 throughout the experiment. Additional muscle relaxants may be administered if necessary. Respiration must be avoided at all times, since otherwise our results would be unusable.

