### **2.1.2 Assessment of the benefit/risk relationship for the patient.**

HFNCT and apnoeic oxygenation are concepts that have been provided with enough evidence to sustain their acceptance in clinical use. There have even been studies suggesting possibility of oxygenation, using very low flows of oxygen [7-9]. But both, high flow and low flow have never been directly compared for its influence on human physiology. However small the risk, desaturation in low-flow groups cannot be completely ruled out. But one of our endpoints is saturation of <92% after which the experiment will be discontinued. Saturation of 92% does not lead to any ischemic damage in healthy patients and all patients with known risks or vulnerability of ischemic events are excluded.

Furthermore,  $p_a\text{CO}_2$  will rise, this leads to a cerebral vasodilation. There is no data setting any threshold after which potential damage would occur, even though patients with  $p_a\text{CO}_2$  up to 250 mmHg have been shown to recover without any neurological impairment [4]. Our limit will be set at 80 mmHg, which therefore should not lead to any neurological damage whatsoever, especially since all patients with high vulnerability towards hypercapnia are excluded. Measuring near infrared spectroscopy (NIRS) will furthermore ensure, that cerebral perfusion will stay within normal limits.

$\text{CO}_2$  is known to have haemodynamic influence [10, 11], but our pilot data suggest that anaesthetic drugs like Propofol and Remifentanyl overrule this effect, as median blood pressure never exceeded 80mmHg.

Patients safety will not be compromised during the study time, as this procedure has shown to prevent desaturation up to 65 minutes [2, 12]. If unexpected difficult airway should occur in these patients, there is more time for securing the airway until desaturation will set in.

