According to randomization, the intervention will be applied. If jaw thrust is performed, upper airway patency will be visually confirmed using nasopharyngeal fiberscope (EF-N slim, Acutronic, Hirzel, Switzerland). In most cases this should be the case [18]. If not, an oropharyngeal airway (Guedel) will be inserted, and if necessary, manual assistance performed to obtain the required result. If, despite these interventions, the airway is not patent, the study will end prematurely (drop-out). This is very unlikely to happen.

After confirmation of upper airway patency, the experiment will be continued until one of the following criteria is met: SpO2 < 92%, ptcCO2 > 80 mmHg, pH < 7.1, K > 6.0 mmol/l or apnoea-time > 15 minutes.

During the intervention, we will continuously measure arterial blood pressure, pulse oximetry, ptcCO2, ptcO2, heart rate, depth of anaesthesia (Narcotrend™), brain oxygenation, cardiac output by pulse contour analysis, and ventilation distribution changes by thoracic electrical impedance tomography (EIT). Latter will be measured with a PulmoVista® 500, by Dräger, Lübeck, Germany. Furthermore, we will take arterial blood samples at the onset of apnoea, one minute after apnoea, and thereafter every two minutes to perform blood gas analysis (total of max. 10 measurements).

During the experiment, one anaesthesia staff member will be free of all study related responsibilities in order to ensure the patient's wellbeing during anaesthesia consisting of stable blood pressure, neuromuscular blockage, and anaesthesia depth.

The experiment stops, if one of the following criteria is met: SpO2<92%, ptcCO2>80 mmHg, pH<7.1, K>6.0 mmol/l, t >15 minutes. Thereafter the airway will be secured in the planned manner and anaesthesia will continue without any further interruptions.

Patients will be visited before discharge on the first postoperative day or contacted by phone, and asked for any sort of pain (throat, mandibular joint, head, etc.), nausea, vomiting, nasal dryness, lip injuries, dental damages, other injuries, or any other discomfort or complication using a (modified) visual analogue scale (VAS), where 0 is no pain (or discomfort), and 10 is maximum pain (or discomfort) where applicable. We will also assess all kinds of injuries obtained during anaesthesia.

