### 8.5.2 Assessment of secondary outcomes

Time to desaturation below 92% will be measured using a stopwatch. If desaturation does not set in, the experiment will end once 15 minutes have been completed.

Arterial blood pressure will be measured using a catheter in the radial artery. ECG and pulse oximetry will also be measured. These measurements are normal anaesthesia care.

From the arterial catheter blood samples will be drawn for blood gas analyses.

Brain oxygenation as a surrogate of brain perfusion will be assessed by cerebral NIRS, using Niro-200NX (Hamamatsu, Tokyo, Japan) monitor continuously. This is also a standard procedure without complications, especially during cardiac surgery.

EIT will be continuously measured using PulmoVista® 500 by Dräger, Lübeck, Germany, to visualize possible atelectasis and its progression over time.

EIT is a non-invasive, radiation-free technique for the assessment of spatial and temporal ventilation distribution based on the changes in electrical properties of the tissue during the respiratory cycle. EIT measurements will be performed using a commercially available setup (PulmoVista 500, Draeger, Germany). A loose-fitting belt with 16 evenly spaced electrodes will be placed around the participant's chest in thoracic median plane. Small electrical currents are injected through adjacent electrodes in a rotating mode. Resulting potential differences are measured, and impedance distribution sampled at 30 Hz will be calculated by an automated linearised newton-raphson reconstruction algorithm [19]. Relative change in end-expiratory lung impedance (EELI) and measures of ventilation inhomogeneity such as the global inhomogeneity index (GI) will be calculated as described previously using customized software (Matlab R2013a, The MathWorks Inc., Natick, MA, USA) [20, 21].

After securing the airway, the highest etCO2 measured during the first minute will be recorded.

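### The secondary objective of mean apnoea duration is a mean capped at 15 minutes that mixes oxygenation failure with CO2, pH and potassium stops, and it matches neither the listed outcome nor the stated hypothesis

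*Protocol*

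**What the plan says.** The overall objective (4.1) concerns "nasal cannula therapy at different flow rates to prolong the apnoea time during induction of anaesthesia", and the synopsis also asks whether flow rate affects apnoea time. Section 4.3 turns this into a measure: "Secondary study objective is to evaluate the mean duration of apnoea".

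Section 6.1 gives five conditions, and whichever occurs first ends the run: "SpO 2 < 92%, p tc CO 2 > 80 mmHg, pH < 7.1, K > 6.0 mmol/l or apnoea-time > 15 minutes". The time limit appears again in section 8.5.2: "If desaturation does not set in, the experiment will end once 15 minutes have been completed".

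On expected tolerance, 2.1.2 says of the technique that "this procedure has shown to prevent desaturation up to 65 minutes". For the lower flows it says: "However small the risk, desaturation in low-flow groups cannot be completely ruled out". No desaturation rate is given for any arm.

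Two other sections address the same question with different quantities. The outcome list in 5.2 has no mean duration. It has seconds until SpO2 falls to 92%, should that happen, and the lowest saturation. The secondary hypothesis in 10.1 concerns how many patients fail to tolerate 15 minutes, without distinguishing the reason.

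**The concern.** The quantity in 4.3 is the smaller of 15 minutes and the time of the first physiological stop. This causes two problems.

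- **Ceiling.** Where tolerance exceeds 15 minutes, the mean mostly restates the time limit. Arms whose true tolerance differs widely can then give nearly equal means.
- **Mixed causes.** Only the SpO2 stop measures oxygenation. The CO2 stop depends on the rate of CO2 rise, which is the primary outcome, and on the starting level. The pH stop also follows CO2. A shorter mean duration therefore need not mean that oxygenation failed sooner.

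What is at stake is how a secondary result is interpreted. Similar means could be taken as evidence about apnoea tolerance in general, and a difference could be credited to oxygenation when CO2 produced it. Because 4.3, 5.2 and 10.1 define three different quantities, the protocol does not settle which one answers the apnoea-time question.

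**Working it through.** **1. The plan's own figure.** The protocol gives no figure for mean apnoea duration. Its only calculation is the primary sample size (10.2: margin 0.3, SD 0.35, one-sided alpha 0.025, power 80%). It reproduces: 2 × (1.960 + 0.842)² × 0.35² / 0.3² = 21.4, so 22 per group. This point does not affect it.

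**2. Effect of the 15-minute cap alone.** Assume tolerance T is log-normal with median m and log-SD s = 0.3 (the protocol gives no distribution). With Φ the standard normal distribution function:

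E[min(T,15)] = m·exp(s²/2)·Φ((ln(15/m) − s²)/s) + 15·(1 − Φ(ln(15/m)/s))

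For m = 20: 20.92 × Φ(−1.259) + 15 × (1 − Φ(−0.959)) = 20.92 × 0.104 + 15 × 0.831 = 14.64.

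| Assumed median (min) | Capped mean (min) | Desaturating before 15 min |
|---|---|---|
| 20 | 14.64 | 17% |
| 25 | 14.93 | 4% |
| 30 | 14.99 | 1% |
| 60 | 15.00 | 0% |

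A three-fold difference in median (20 v 60) appears as 15.00 − 14.64 = 0.36 min.

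**3. Cap plus CO2 stop, across a wider range of tolerance.** Observed duration was simulated as the smallest of T, time to 80 mmHg and 15 min. CO2 rise was N(1.8, 0.35), from 10.2. Assumptions: starting pCO2 N(40, 4) and log-SD 0.5. Power is for a two-sided 5% t-test with 25 per arm.

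| Median tolerance (min) | Observed mean (min) | Power v a 65-min arm |
|---|---|---|
| 8 | 8.60 | about 100% |
| 12 | 11.42 | about 100% |
| 20 | 13.95 | about 78% |
| 30 | 14.74 | about 5% |
| 65 | 14.97 | – |

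The mean works when desaturation falls inside the window and fails when it falls outside. For 30 v 65 min, true means of about 34 and 73 min differ by about 39 min, but the observed means differ by about 0.2 min.

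**4. Does the CO2 limit act before 15 minutes?** At mean values it does not. From the arterial range of 35–46 mmHg cited in 10.2, at 1.8 mmHg/min, the 15-minute value is 35 + 27 = 62 to 46 + 27 = 73 mmHg. The 80 mmHg limit is reached at (80 − 46)/1.8 = 18.9 to (80 − 35)/1.8 = 25 min.

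Between-patient variation changes this. With starting value N(b, 4) and rise N(r, 0.35), the 15-minute value has mean b + 15r and SD √((15 × 0.35)² + 4²) = 6.60. With no desaturation at all:

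| Assumed start b (mmHg) | Early CO2 stop, r = 1.8 | Early CO2 stop, r = 2.1 (1.8 plus the margin) |
|---|---|---|
| 40 | z = (80 − 67)/6.60 = 1.97, 2% | z = (80 − 71.5)/6.60 = 1.29, 10% |
| 45 | z = (80 − 72)/6.60 = 1.21, 11% | z = (80 − 76.5)/6.60 = 0.53, 30% |
| 50 | z = (80 − 77)/6.60 = 0.45, 32% | z = (80 − 81.5)/6.60 = −0.23, 59% |

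In the 45 mmHg row, the simulated mean durations are 14.85 and 14.50 min, a gap of about 0.35 min with identical oxygenation. That is about the size of the gap in step 2 from a three-fold difference in tolerance.

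**5. pH limit.** By the Henderson–Hasselbalch relation, with solubility 0.0307 and pK 6.1, pH 7.10 corresponds to pCO2 = bicarbonate/0.307. Assumed bicarbonate of 22, 24 and 26 mmol/l gives 72, 78 and 85 mmHg. The lowest value lies inside the 62–73 mmHg range of step 4, so this stop can also act within the window. Neither the pH nor the potassium stop was simulated.

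**The case against.** Much of the case on the other side stands.

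- A reader might infer that mean apnoea duration cannot be measured at all. The documents do not support that. Duration up to 15 minutes is observable, SpO2 below 92% is one of the stops, and step 3 shows that early desaturation would be detected.
- A reader might also infer that tolerance far beyond 15 minutes is expected in every arm. The 65-minute figure is an upper extreme, which 3.1 attributes to the high-flow technique. It is not an expected value for 10 or 2 l/min, and 2.1.2 leaves desaturation at low flow open. The medians used above are assumptions.
- Measures bounded at 15 minutes already exist: time to desaturation within the predefined period (synopsis and 5.2) and the 10.1 count. Analysis detail for stopped runs may properly sit in an analysis plan that is not shown. However, the choice of quantity in 4.3, and its mismatch with 5.2 and 10.1, are in the protocol itself.
- The CO2 stop is secondary to the time limit at normal starting values. Starting CO2 precedes the intervention, so under randomisation it differs between arms only by chance. This does not cover the rate of rise, which the intervention may change and which drives the contrast in step 4.
- Replacing the mean with the proportion completing 15 minutes would not help on its own. It has the same ceiling and is slightly less sensitive: for 20 v 60 min with 25 per arm, about 24% power (Fisher's exact test) against about 31% for a t-test on the capped mean.

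No section commits to concluding that flow has no effect on apnoea time. The risk is a misreading that the wording permits.

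**Conclusion.** The point holds in a limited form. The 4.3 objective is a mean truncated at 15 minutes that pools oxygenation failure with CO2, pH and potassium stops. It is informative when many patients desaturate within the window and uninformative about tolerance beyond it. It can also differ between arms because of the primary outcome alone: about 11% v 30% early CO2 stops at 1.8 v 2.1 mmHg/min from an assumed 45 mmHg. The sizes depend on the assumed tolerance distributions and starting CO2. The truncation, the pooling of stop reasons and the mismatch between 4.3, 5.2 and 10.1 follow from the text alone.

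It would be wrong to conclude that the 15-minute limit or any other stopping limit is at fault, or that the trial's main result is affected. This is a free improvement to a secondary objective.

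**What to change.** 1. In 4.3, replace the plain mean with time to SpO2 below 92%, administratively censored at 15 minutes, with CO2, pH and potassium stops as competing events. Report cumulative incidence per arm with 95% confidence intervals.
2. For 10.1, report the number of patients not completing 15 minutes in each arm by stop reason, with oxygenation stops separate from the others.
3. Use the same definition in 4.3, 5.2 and 10.1.
4. In 4.1 and the synopsis, limit apnoea-time conclusions to a period of up to 15 minutes.

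This does not recover tolerance beyond the cap, and no design that keeps the cap could. It removes the misattribution and narrows the claim to what is observed. The cost is wording: time, SpO2, transcutaneous CO2 and blood gases are already measured, so the stop reason can be established from planned data. The stopping limits, primary outcome and sample size stay as they are.

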### **4.4 Safety Objectives**

Saturation using simple pulse-oximetry will be closely monitored and any desaturation below 92% will lead to immediate discontinuation of the experiment. NIRS will be measured to register all changes in cerebral blood flow that might be triggered by increased  $p_aCO_2$ . Arterial blood gas analysis will be conducted every two minutes to detect severe acidosis (pH <7.10) as well as hyperkalaemia (K >6.0 mmol/l).

## **5. STUDY OUTCOMES**

### **5.1 Primary Outcome**

Primary outcome: increase of  $p_{tc}CO_2$  level in mmHg/min during apnoea.

## 5.2 Secondary Outcomes

Secondary outcomes:

- Seconds until desaturation from SpO2 100% to 92% measured by pulse oximetry (if occurring at all)
- Lowest saturation
- ptcO2 rise in mmHg/min
- Airway patency (yes/no)
- Vital parameters (BP, HR, SpO2)
- Arterial pH, paCO2 and paO2
- Cerebral Oxygenation (NIRS)
- Highest etCO2 measured in the first minute after securing airway in mmHg
- TOF
- Cardiac output
- Changes in lung volume measured by EIT

## 5.3 Safety Outcomes

Arterial blood gas analysis will be conducted every two minutes to detect severe acidosis (pH <7.10) or hyperkalaemia (>6.0 mmol/l).

## 6. STUDY DESIGN

### 6.1 General study design and justification of design

Single blinded randomised controlled prospective trial (High-flow 70 l/min using two different techniques, medium-flow 10 l/min and low-flow 2 l/min, each with 100% oxygen).

Four interventions will be applied.

- High-flow nasal cannula oxygen **70** l/min using OptiFlow™ system by Fisher&Paykel™ and an oxygen inspiration concentration FiO2 of 100%, with continuous laryngoscopy
- High-flow nasal cannula oxygen **70** l/min using OptiFlow™ system by Fisher&Paykel™ and an oxygen inspiration concentration FiO2 of 100%, performing jaw thrust
- Medium-flow nasal cannula oxygen **10** l/min using Carbamed digiflow, Aquapak Hudson RCI to humidify oxygen and standard nasal cannula with 100% oxygen, performing jaw thrust
- Low-flow nasal low-flow oxygen **2** l/min using Carbamed digiflow, Aquapak Hudson RCI and standard nasal cannula with 100% oxygen, performing jaw thrust

The departmental digital Anaesthesia Information System (AIS) will be used to screen patients for compatibility.

Once written informed consent is obtained, after patients were given enough time to validate their participation and considering all possibilities, and pregnancy has been excluded in female patients (in all female patients: pregnancy test before inclusion), the patient will be brought to the operating theatre. After local anaesthesia, an arterial cannula will be placed

into the radial artery and arterial blood gases will be drawn. All necessary monitoring (EKG, pulse oximetry, EIT, NIRS, Narcotrend™, transcutaneous pCO2) will be installed and pre-oxygenation will begin. Once etO2 has reached 90% or more than three minutes have passed, induction of anaesthesia will begin using a TCI system for both Propofol and Remifentanyl. For neuromuscular blockage, Rocuronium 0.9mg/kg will be administered.

After induction of general anaesthesia confirmed by absent respiratory movement, unconsciousness, and according to Narcotrend™-values; mask ventilation will commence. If for whatever reason mask ventilation is still impossible after full relaxation and placement of a Guedel tube, the experiment will be discontinued immediately, and the airway will be secured by the anaesthetist.

According to randomization, the intervention will be applied. If jaw thrust is performed, upper airway patency will be visually confirmed using nasopharyngeal fiberscope (EF-N slim, Acutronic, Hirzel, Switzerland). In most cases this should be the case [18]. If not, an oropharyngeal airway (Guedel) will be inserted, and if necessary, manual assistance performed to obtain the required result. If, despite these interventions, the airway is not patent, the study will end prematurely (drop-out). This is very unlikely to happen.

After confirmation of upper airway patency, the experiment will be continued until one of the following criteria is met: SpO2 < 92%, ptcCO2 > 80 mmHg, pH < 7.1, K > 6.0 mmol/l or apnoea-time > 15 minutes.

During the intervention, we will continuously measure arterial blood pressure, pulse oximetry, ptcCO2, ptcO2, heart rate, depth of anaesthesia (Narcotrend™), brain oxygenation, cardiac output by pulse contour analysis, and ventilation distribution changes by thoracic electrical impedance tomography (EIT). Latter will be measured with a PulmoVista® 500, by Dräger, Lübeck, Germany. Furthermore, we will take arterial blood samples at the onset of apnoea, one minute after apnoea, and thereafter every two minutes to perform blood gas analysis (total of max. 10 measurements).

During the experiment, one anaesthesia staff member will be free of all study related responsibilities in order to ensure the patient's wellbeing during anaesthesia consisting of stable blood pressure, neuromuscular blockage, and anaesthesia depth.

The experiment stops, if one of the following criteria is met: SpO2<92%, ptcCO2>80 mmHg, pH<7.1, K>6.0 mmol/l, t >15 minutes. Thereafter the airway will be secured in the planned manner and anaesthesia will continue without any further interruptions.

Patients will be visited before discharge on the first postoperative day or contacted by phone, and asked for any sort of pain (throat, mandibular joint, head, etc.), nausea, vomiting, nasal dryness, lip injuries, dental damages, other injuries, or any other discomfort or complication using a (modified) visual analogue scale (VAS), where 0 is no pain (or discomfort), and 10 is maximum pain (or discomfort) where applicable. We will also assess all kinds of injuries obtained during anaesthesia.

Overall, we will include 100 patients, 25 per group. Patients will be blinded as to their group allocations. Double-blinding is not possible, as devices differ from each other.

This design allows us to focus our study on the primary outcome, since we ensure, that free air circulation (and possible CO2 clearance) is possible by visually assessing airway patency. Through measurement of extended vital parameters, we can identify physiologic influence of rising CO2 in anaesthetized patients undergoing apnoeic oxygenation.

In addition, demographic data will be extracted from the AIS. This only includes standard data, that is collected through routine normal clinical workflow, such as age, sex, weight, height, BMI, airway risk factors, underlying diseases, smoking habits, ASA physical health status and indication for the surgery.

